### Aim 2: Evaluate New, Single-Session, Virtual Reality Growth Mindset Intervention

As for Aim 1, we will use mixed-effects linear models to test the hypothesis that VR-GMI predicts greater reductions in adolescent and parent-reported depressive symptom severity (primary study outcomes), as well as perceived primary and secondary control, hopelessness, loneliness, attitudes toward psychotherapy, and parent psychopathology (secondary outcomes), relative to (1) the Web-based GM program, (2) the control program, and (3) either program, when combined into a single, *non-VR intervention* group. Models will be structured as described in Aim 1. A significant (*P*<.05) interaction between the second orthogonal contrast mentioned in Aim 1 and time would indicate that interventions teaching GM predicted significantly different 9-month change in an outcome relative to the control ST condition. We will also replicate these analyses for the most central symptoms of adolescent depression identified in previous analyses (*sadness*, *self-hatred*, and *loneliness* [43]) and use Holm-Bonferroni corrections for multiple comparisons.

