Notably, a recent systematic review of studies evaluating VR applications for mental health identified only 2 studies that have tested immersive VR mental health treatment approaches; both were uncontrolled feasibility trials targeting adults [19]. Thus, to our knowledge, this study will be the first randomized trial evaluating a brief VR intervention for adolescent depressive symptoms.

This research has 4 specific aims. Our first aim is to replicate past research suggesting that GM SSIs can significantly reduce depressive symptoms in at-risk adolescents. We hypothesize that adolescents aged 12 to 16 years who participate in a GMI (Web-based *or* VR–based) will show larger reductions in depression symptoms from baseline through the 9-month follow-up assessment compared with adolescents who receive an active, Web-based control program.

Our second aim is to evaluate new, single-session, VR GMI including a comparative efficacy study. Our second aim is to also evaluate whether the new VR–based GM SSI (the VR Personality Project) can reduce depressive symptoms in adolescents, both relative to an active control program and to the previously tested Web-based GM SSI [13,14]. We hypothesize that adolescents who participate in the VR–based GM SSI will show larger reductions in depressive symptoms from baseline through the 9-month follow-up assessment compared with adolescents who receive the Web-based GMI *and* compared with adolescents who receive the active Web-based control program.

Our third aim is to test whether shifts in perceived control mediate intervention effects on adolescent depressive symptoms. The VR Personality Project was designed to target and increase adolescents’ perceived control by offering a more immersive, active, and user-directed intervention experience than the Web-based GM SSI can provide. Thus, the third goal of this study is to examine whether the VR Personality Project does, in fact, reduce adolescent depressive symptoms by eliciting proximal increases in perceived control. We hypothesize that the VR Personality Project will lead to larger increases in immediate postintervention perceived control than the Web-based intervention from pre- to postintervention and that these increases will mediate subsequent reductions in adolescent depression across the follow up period.

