## Results

### Aim 1: Attempt to Replicate Past Research

We will use mixed-effects linear models to test the hypothesis that interventions teaching GM (either VR or Web-based) predict reductions in adolescent depressive symptom severity (primary study outcome), per both adolescent and parent reports, relative to Web-based ST. Our study design, including 3 assessment points is structured to allow for detection of linear intervention effects. We will run additional mixed-effects linear models to assess whether interventions teaching GM predict larger improvements in secondary study outcomes (perceived primary and secondary control, hopelessness, loneliness, attitudes toward psychotherapy, and parent psychopathology) versus Web-based ST. Intervention condition will be a binary predictor variable in these models, with the VR GMI and Web-based GMI groups collapsed into a single *GM* intervention group. Potential covariates will include family income, age, sex, and time (baseline, postintervention where applicable, and 3-month and 9-month follow-up); each possible covariate will be included in analyses if it shows a significant association with a model outcome at baseline or any follow-up point (such associations are unlikely to occur, given randomization procedures, but remain possible). Models will include a random intercept and slope, an autoregressive error structure, and use full information maximum likelihood (FIML) estimation to address missing data. We will create 2 orthogonal planned contrasts for testing intervention effects. One planned contrast will examine whether the 2 active GM conditions differ from the ST control condition, whereas the other planned contrast will examine whether the VR-based intervention outperforms the Web-based intervention. A significant (*P*<.05) interaction between the first contrast and time would indicate that interventions teaching GM predicted significantly different 9-month change in an outcome relative to the control ST condition. We will also replicate these analyses for the most central symptoms of adolescent depression identified in previous analyses (*sadness*, *self-hatred*, and *loneliness*) and use Holm-Bonferroni corrections for multiple comparisons.

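### Aim 2's decision rule attaches a growth-mindset-versus-control conclusion to the contrast that compares VR with Web-based delivery

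*Protocol article*

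**What the plan says.** All references are to the protocol article.

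- **Aim 1, contrasts.** The plan announces the pair: "We will create 2 orthogonal planned contrasts for testing intervention effects". The first is given as "One planned contrast will examine whether the 2 active GM conditions differ from the ST control condition". For the second, "the other planned contrast will examine whether the VR-based intervention outperforms the Web-based intervention".
- **Aim 1, decision rule.** The threshold is P<.05, and the rule reads: "interaction between the first contrast and time would indicate that interventions teaching GM predicted significantly different 9-month change in an outcome relative to the control". The comparator is ST, so contrast and conclusion agree.
- **Aim 2, decision rule.** At the same threshold, the rule reads: "interaction between the second orthogonal contrast mentioned in Aim 1 and time would indicate that interventions teaching GM predicted significantly different 9-month change". The sentence ends by naming the comparator; its conclusion in full is "interventions teaching GM predicted significantly different 9-month change in an outcome relative to the control ST condition".
- **Aim 2, hypotheses.** The opening of the same section lists three comparisons for the VR intervention: against the Web-based GM program, against the control program, and against those two combined. The second aim under Objectives also hypothesises larger reductions with VR than with the Web-based GM program and "compared with adolescents who receive the active Web-based control program".
- **Aim 1, coding.** The plan states: "Intervention condition will be a binary predictor variable in these models, with the VR GMI and Web-based GMI groups collapsed into a single". The merged group is labelled GM. Aim 2 says that its models follow the Aim 1 structure.

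**The concern.** Aim 2 names one contrast and draws the conclusion that belongs to the other. The second contrast compares the two GM arms with each other, so a significant result says that delivery format matters. It does not say whether teaching GM differs from ST.

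This is the only decision rule written for Aim 2, the aim that evaluates the new intervention, and it covers the depression outcome. Taken literally, a VR-versus-Web result would be published as evidence on GM against control. If analysts instead follow the evident intent, they depart from the written rule, and a critic can say that the interpretation was settled after the data were seen.

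**Working it through.** **The plan's own figure.** The sample-size section gives 969, 159 and 66 for an omnibus one-way ANOVA in three arms (alpha .05, power .80). A noncentral F calculation with noncentrality N × f² and f = 0.10, 0.25 and 0.40 returns the same three totals, with power 0.801, 0.805 and 0.818. The figures reproduce. The point does not depend on them; they supply only the 53 per arm used below.

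**Contrast weights.** Order the arms as (VR, Web GM, ST) and apply the weights to each arm's change:
- c1 = (0.5, 0.5, -1), from Aim 1
- c2 = (1, -1, 0), from Aim 1
- c1 · c2 = 0.5 - 0.5 + 0 = 0, so they are orthogonal, as the plan says

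The ST weight in c2 is 0. A c2 by time interaction therefore estimates no difference from ST. ST data can still enter through the pooled variance.

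**Aim 2's three comparisons in terms of the contrasts:**

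| Comparison | Weights | Expression |
|---|---|---|
| VR vs Web GM | (1, -1, 0) | c2 |
| VR vs ST | (1, 0, -1) | c1 + 0.5 × c2 |
| VR vs Web GM and ST combined | (1, -0.5, -0.5) | 0.5 × c1 + 0.75 × c2 |

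Check of the second row: (0.5 + 0.5, 0.5 - 0.5, -1 + 0) = (1, 0, -1). Check of the third: (0.25 + 0.75, 0.25 - 0.75, -0.5 + 0) = (1, -0.5, -0.5).

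The conclusion in the Aim 2 rule, pooled GM against ST, is c1. It is none of the three rows.

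**How often the wrong conclusion would arise.** The document does not give the arm means, so these are assumed. The setting is standardised change with SD 1, 53 per arm, no dropout, two-sided alpha .05 and 159 - 3 = 156 degrees of freedom. Higher values mean more improvement. This is a noncentral t illustration, not the planned mixed model.

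- SE(c1) = √(1.5/53) = 0.168
- SE(c2) = √(2/53) = 0.194

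| Assumed means (VR, Web, ST) | c1 | P(c1 significant) | c2 | P(c2 significant) |
|---|---|---|---|---|
| A: 0.25, -0.25, 0 | 0 | 0.05 | 0.5 | 0.73 |
| B: 0.5, 0.5, 0 | 0.5 | 0.84 | 0 | 0.05 |
| C: 0.5, 0, 0 | 0.25 | 0.31 | 0.5 | 0.73 |

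In A the pooled GM arms equal ST, yet the Aim 2 rule would declare a GM-versus-ST difference in about 73% of trials. In C the Web GM arm does no better than ST and only VR works. The rule would still credit GM interventions as a class in about 73% of trials, although the contrast that tests that statement is significant in about 31%. In B the second contrast is significant at the nominal 5%.

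**The case against.** The best defence is that the intent can be recovered. Aim 1 defines the second contrast correctly, and Objectives and the first sentence of Aim 2 both state the VR-versus-Web hypothesis. The faulty ending repeats the end of the Aim 1 rule, so it is probably carried-over text, and a careful analyst would notice. In scenario A, the Aim 1 result would usually conflict visibly with the Aim 2 claim. This limits the practical risk, but it does not make the written rule right, and nothing elsewhere in the article corrects it.

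The defence does hold against several stronger readings that a reader might infer:

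- **That a significant result would be reported as GM beating control.** The rule speaks of significantly different change, not of superiority.
- **That the rule would deny a real GM effect when VR and Web work equally well.** The Aim 2 sentence says nothing about a non-significant result, and Aim 1 keeps its own correct GM-versus-ST rule. In scenario B that rule detects the effect about 84% of the time.
- **That VR versus Web has no decision rule.** The contrast, its interaction with time and the P<.05 threshold are all stated. Only the conclusion is wrong.
- **That the collapsed binary predictor makes VR versus Web inestimable and must be dropped.** The binary coding is tied to the Aim 1 models of GM against ST, where pooling is legitimate. Aim 2's reference to the Aim 1 structure can fairly be read as meaning the random effects, error structure, estimation and covariates. A clearer statement of the Aim 2 coding is enough.
- **That VR versus ST has been left out.** Aim 2 names it as a comparison within mixed models. It is true only that neither planned contrast tests it. An article may leave the exact estimating term to a fuller document.

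**Conclusion.** The point holds as a direct contradiction between two sections. Aim 2 draws a GM-versus-ST conclusion from a contrast that Aim 1 defines as VR versus Web GM. This rests on the text and the contrast weights and needs no numerical assumption.

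Its size depends on the true arm differences. If all three arms are equal, the rule misleads at no more than the nominal 5%. If VR and Web differ by 0.5 SD while the pooled GM arms equal ST, it misleads in about 73% of trials under the stated simplifications. The error runs in one direction: a format difference is reported as a GM-versus-control difference. It does not remove the Aim 1 test, the VR-versus-Web test or the sample-size basis.

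**What to change.** 1. **Required.** Replace the Aim 2 rule with: *A significant (P<.05) second contrast × time interaction would indicate that VR GMI and Web-based GMI differ in 9-month change.* Leave the GM-versus-ST conclusion to the first contrast.
2. **Clarification.** State that the Aim 2 models code condition as three arms with both contrasts. The binary GM/ST predictor can stay for Aim 1.
3. **Clarification.** Estimate VR versus ST from that three-arm model as contrast 1 + 0.5 × contrast 2, and test its interaction with time at the same P<.05. The comparison with the combined non-VR group is available from the same model as 0.5 × contrast 1 + 0.75 × contrast 2.

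One point for the programmer: these multipliers apply to the contrast values, that is, the weights (0.5, 0.5, -1) and (1, -1, 0) applied to arm-specific change. If the same numbers are entered as predictor codes with coefficients b1 and b2, then VR minus ST is (0.5 + 1) × b1 + (1 - 0) × b2 = 1.5 × b1 + b2.

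The cost is one replaced sentence and a line or two of model wording, with no change to sample size, assessments or data collection.

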### Aim 3: Test Mediation Through Perceived Control

To test whether the VR intervention and the Web-based GM intervention reduces youth-reported depressive symptoms through proximal increases in perceived control, we will conduct multiple mediation analyses which involve simultaneous indirect effects by multiple variables [44]. This approach allows for both an analysis of the total indirect effect (the aggregate indirect effect of all the candidate mediators under investigation) and analyses of specific indirect effects (ie, of each mediator under investigation). For mediation models assessing perceived control, we will use postintervention data to assess candidate mediators and 9-month follow-up data to assess depressive symptoms. In each model, the predictor variable will be intervention condition (in Model 1, VR versus Web-based GM intervention; in Model 2, VR versus Web-based ST; and in Model 3, Web-based GM versus Web-based ST); the simultaneous mediator variables will be postintervention perceived behavioral control and postintervention perceived emotional control. We will use bias-corrected bootstrapping to test the significance of specific and total indirect effects within the mediation model. Bootstrapping has the advantage of high statistical power without assuming multivariate normality in sampling distributions, enabling parsimonious analysis of one or several candidate mediators [44,45]. The Iavaan package version 0.5-16 in R version 2.15.1, which is capable of testing both multiple and single mediator models using FIML estimation, will be used for mediation tests [46]. To test for indirect effects of candidate mediators, parameter estimates of total and specific indirect effects are generated, along with their CI, using 1000 to 20,000 random bootstrapped samples. We will specify 5000 resamples in this study per Preacher and Hayes’ [32] recommendations. If the 95% bias-corrected CI for a total indirect parameter estimate does not contain 0, then that indirect effect can be considered statistically significant, demonstrating mediation [44,45]. Using this approach, this study will be sufficiently powered to detect significant indirect effects in each model (bias-corrected CIs for a 2-mediator model show .80 power for samples of 50 and over .90 for samples of 100 [46,47]).

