### Follow-Up Assessments

To enable evaluation of the interventions’ effects on depressive symptoms and secondary study outcomes over time, each adolescent and parent will be invited to complete Qualtrics-based questionnaire batteries, including the same questionnaires as those they completed at their initial laboratory session. Links to Qualtrics surveys will be sent to families at 3- and 9-month follow-up points. Surveys may be conducted via phone at the family’s request. Families who do not complete the follow-up questionnaires within 3 days of receipt will receive up to 3 reminder messages from the research team to encourage survey completion.

Notably, logistical constraints necessitated our limiting the number of follow-up assessments in this study to 2 per family (at 3- and 9-month postintervention), and analyses were planned accordingly (see below for a more thorough description). We elected a final follow-up assessment at the 9-month mark to maintain consistency with previous trials of GMI [13,14].

After the study is complete, an aggregate results summary will be emailed to families. Condition assignment will be revealed at this time, and all youths will receive access to both Web-based interventions. Youths who did not receive the VR program will be invited to complete the intervention at Stony Brook University.

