#### Children’s Depression Inventory-2

Adolescent depressive symptom severity will be assessed using the CDI-2 [31] child form (youth-report) and parent forms (parent-report). The CDI-2 is a reliable, valid measure of youth depression severity, normed for youth age and sex and yielding raw and *T* scores. Changes in youth-report CDI-2 scores from baseline to each of the follow-up assessments (3-month and 9-month) will serve as the primary index of intervention effects. Changes in parent-report CDI-2 scores from baseline to each of the follow-up assessments (3-month and 9-month) will serve as a secondary index of intervention effects. The CDI-2 will not be administered to youths or to parents immediately postintervention, as we do not expect depressive symptom change to occur within the span of 1 study session. Changes in scores on other assessments will serve as secondary outcomes.

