**Assessments**								
	**Youth self-report**						
		Children's Depression Inventory 2-Youth	—	X	—	—	X	X
		Screen for anxiety related disorders-Youth	—	X	—	—	X	X
		Primary control scale for children	—	X	—	X	X	X
		Secondary control scale for children	—	X	—	X	X	X
		Beck Hopelessness Scale-Short form	—	X	—	X	X	X
		UCLA^f^ Loneliness Scale-Version 3	—	X	—	X	X	X
		Implicit personality theories questionnaire	—	X	—	X	X	X
		Attitudes toward therapy scale	—	X	—	X	X	X
		Program feedback scale	—	—	—	X	—	—

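### The Aim 3 mediation models take only 9-month depression as outcome, so the 3-month part of the stated hypothesis is not tested

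*Protocol article*

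**What the plan says.** Under Objectives, the third aim first predicts larger immediate gains in perceived control with the VR programme than with the Web-based one. It then predicts that "these increases will mediate subsequent reductions in adolescent depression across the follow up period".

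The Children's Depression Inventory-2 section fixes the efficacy measure: "Changes in youth-report CDI-2 scores from baseline to each of the follow-up assessments (3-month and 9-month) will serve as the primary index". The schedule in Table 2 marks the youth CDI-2 at baseline, 3 months and 9 months.

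The Aim 3 analysis section narrows the outcome: "we will use postintervention data to assess candidate mediators and 9-month follow-up data to assess depressive symptoms". This covers every comparison: "in Model 1, VR versus Web-based GM intervention; in Model 2, VR versus Web-based ST; and in Model 3, Web-based GM versus Web-based ST". The mediators are postintervention perceived behavioural and emotional control, entered together. Indirect effects are tested with bias-corrected bootstrap intervals, in software chosen for its full information maximum likelihood (FIML) estimation. The section describes no mediation model for the 3-month score or for the symptom trajectory.

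**The concern.** The hypothesis refers to the follow-up period and the primary index names two visits, but the only mediation test uses the later one. The mediator is measured directly after a session of about 30 minutes. The 3-month CDI-2 is the first depression score after it. Outside treatment is allowed throughout, and every family is offered referral information. An effect of the control shift on symptoms could therefore be visible at 3 months and diluted by 9.

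Raising perceived control is the design rationale of the VR programme. A negative Aim 3 result would be read as evidence against that mechanism, when it might reflect only the choice of visit. There is also a smaller loss of information. FIML uses only the variables in the model, so a youth who answers at 3 months but not at 9 informs the path from condition to mediator and nothing on the outcome side.

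**Working it through.** **The plan's own figures.** The point turns on no stated figure, but the sample size sets the scale. For a one-way ANOVA with k = 3, alpha .05, noncentrality N·f² and f = d/2 = 0.25, N = 159 gives power 0.805. The stated 159 is therefore reproduced, as are 969 (f = 0.10, power 0.801) and 66 (f = 0.40, power 0.818). Each pairwise mediation model has 2 × 53 = 106 youths. The mediation power statement (.80 at 50, over .90 at 100) cannot be reproduced, because no path sizes are given.

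**What a 9-month outcome can detect.** The indirect effect at a visit is the sum over the two mediators of a·b, where a is the effect of condition on the mediator and b is the effect of the mediator on depression at that visit. If b is zero at 9 months, the 9-month indirect effect is zero, whatever happened at 3 months.

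A simulation illustrates the scale. Its inputs are assumptions except where noted:
- 53 per arm (from the article), complete data, 1000 replicates, and a Monte Carlo 95% interval in place of the bias-corrected bootstrap.
- Two unit-variance mediators correlated 0.5, with no direct effect of condition.
- Residual correlation of 0.6 between the 3- and 9-month scores.
- a = 0.5, or a = 0.34. The article reports .34 for perceived control over behaviour in the earlier trial; here it is applied to both mediators.

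| a | b at 3 mo | b at 9 mo | Power, 9 mo | Power, 3 mo | Power, two-visit mean |
|---|---|---|---|---|---|
| 0.5 | 0.2 | 0.2 | 0.64 | 0.63 | 0.69 |
| 0.5 | 0.3 | 0.1 | 0.21 | 0.77 | 0.70 |
| 0.5 | 0.3 | 0 | 0.04 | 0.81 | 0.54 |
| 0.34 | 0.2 | 0.2 | 0.37 | 0.36 | 0.42 |
| 0.34 | 0.3 | 0.1 | 0.11 | 0.48 | 0.41 |

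With a stable effect the choice of visit hardly matters. With a fading effect the 9-month test mostly misses it.

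**Why the two-visit mean should not become the test.** Relative to one visit, the standard error of the mean of two equally variable scores is sqrt((1 + r)/2). With assumed r = .5 this is .866, and with r = .7 it is .922, a cut of 13% or 8%. That is a gain only if the effect is similar at both visits. The Aim 1 section says the design is meant to detect linear effects. If the arms diverge linearly in months from baseline, the 3-month effect is 3/9 = 1/3 of the 9-month effect, and the mean carries (1/3 + 1)/2 = .667 of it. The ratio of signal to standard error becomes .667/.866 = .77 or .667/.922 = .72 of the 9-month value, a loss of 23% to 28%.

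**Missing data.** The article gives no attrition rate. Each percentage point lost between 3 and 9 months is 0.01 × 106 = 1.06 youths per model, so an assumed 10% is 10.6. With complete data, the same predictors for both scores and a free residual covariance, adding the 3-month score leaves the 9-month estimate unchanged. Any precision gain at 9 months therefore comes only from youths missing that score, and it grows with the correlation between visits.

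**The case against.** The strongest reply is that nothing here is contradictory. Aims 1 and 2 define their targets as change through the 9-month visit, and the third aim's wording can be read as the same span. The Aim 1 and Aim 2 sections interpret their decisive tests as 9-month change, so a 9-month mediation outcome explains the effect the trial sets out to show. The article also gives a reason for that visit: "We elected a final follow-up assessment at the 9-month mark to maintain consistency with previous trials of GMI". One late outcome limits multiplicity and places the mediator clearly before the outcome.

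Most of this stands. A single prespecified final-visit outcome is legitimate, and a benefit gone by 9 months is not what the article treats as success. Two parts do not settle the point. The reason quoted explains why 9 months is the last assessment, not why it is the only mediation outcome. A 3-month score also follows the mediator, so time order does not exclude it.

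A reader might infer that the 3-month scores are thrown away. They are not: the Aim 1 mixed models include "time (baseline, postintervention where applicable, and 3-month and 9-month follow-up" among their time points, and Aim 2 uses the same structure. The scores are absent only from Aim 3. Nor will they exist for everyone, since families are invited to online surveys and reminded.

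The full plan might name auxiliary variables for FIML, which an article need not list. If the 3-month CDI-2 were among them, the missing-data part would fall away. The untested 3-month indirect effect would remain.

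**Conclusion.** The concern holds as a mismatch of scope between the third aim and its only test. The stated hypothesis, read with the two-visit primary index, covers 3 months, and the mediation models do not. A mediated benefit that fades would be reported as no mediation. No efficacy test under Aims 1 and 2 and no sample size is affected.

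The size is conditional. It is small if the effect is stable and large if it fades (0.04 to 0.21 at 9 months against 0.77 to 0.81 at 3 months, with a = 0.5). The path sizes, the correlations and the fading pattern are assumptions; the document does not say which pattern to expect.

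A reader might also infer that using both visits cuts the standard error by 8% to 13%, and that their mean should replace the 9-month test. The document does not support this. That figure needs equal effects at both visits, and it concerns the outcome score rather than the indirect effect, which also depends on an unchanged path from condition to mediator. Under the linear pattern anticipated in Aim 1, the mean is the weaker test.

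**What to change.** In each of the three lavaan models, enter the 3-month and 9-month youth CDI-2 jointly as outcomes, with the same predictors and a free residual covariance. Keep the 9-month total indirect effect as the main test. Name the 3-month indirect effect as a prespecified secondary result and report it whatever the 9-month finding. FIML will then also use the 3-month score where the 9-month score is missing.

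If the investigators prefer to keep 9 months alone, the third aim should be reworded to 9-month depression, and a null result should not be described as absence of mediation earlier in follow-up.

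The joint model needs no new data or visits. It costs one extra secondary estimate per model, three in all, with the 9-month test left in place. Any gain in precision cannot be promised in advance, because the article gives neither attrition nor the correlation between visits.

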#### Primary Control Scale for Children

The primary control scale for children (PCSC) [35] is a 24-item scale measuring youths’ perceived ability to influence or alter objective events or conditions through personal effort. Youth rate agreement with statements about their ability to exert primary control (eg, “I can do well on tests if I study hard” and “I can get other kids to like me if I try”). The PCSC has shown acceptable internal consistency, 6-month test-retest reliability, and inverse relations to adolescent depression severity.

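### The Aim 3 mediation models use post-intervention control and 9-month depression without baseline values, so a pre-existing link between control and depression can pass for mediation

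*Protocol article*

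**What the plan says.** The Objectives section of the protocol article states the third aim in terms of change. The VR programme should produce "larger increases in immediate postintervention perceived control than the Web-based intervention from pre- to postintervention", and "these increases will mediate subsequent reductions in adolescent depression across the follow up period". The Aim 3 analysis section opens in the same terms: it will test whether the growth mindset interventions work in a way that "reduces youth-reported depressive symptoms through proximal increases in perceived control".

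The model in that section is built on levels:

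- **Predictor:** "In each model, the predictor variable will be intervention condition", taken pairwise (VR v Web growth mindset, VR v supportive therapy, Web growth mindset v supportive therapy).
- **Mediators:** "the simultaneous mediator variables will be postintervention perceived behavioral control and postintervention perceived emotional control".
- **Timing:** "we will use postintervention data to assess candidate mediators and 9-month follow-up data to assess depressive symptoms".
- **Decision rule:** a 95% bias-corrected bootstrap interval for the total indirect effect that excludes zero is taken to show mediation.

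No baseline control score, baseline CDI-2 or change score is named. The covariate list under Aim 1 (income, age, sex, time) does not contain baseline control. Aim 2 refers back to the Aim 1 model structure; Aim 3 does not. Table 2 shows both control scales and the youth CDI-2 collected at baseline.

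**The concern.** An indirect effect is the product of two paths: condition to control (a) and control to depression (b). Randomisation makes the first comparable between arms. It does nothing for the second, which compares youths with higher and lower post-intervention control within the same arm. Those youths already differed before the session.

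The protocol article itself gives grounds to expect such differences. In the description of the control measure it says: "The PCSC has shown acceptable internal consistency, 6-month test-retest reliability, and inverse relations to adolescent depression severity". Baseline and post-intervention control are also measured within one laboratory visit of about two hours, so substantial carry-over is likely. A model without baselines therefore gives a negative b path even if changing control does nothing to depression. Multiplied by a non-zero a path, this becomes a non-zero indirect effect.

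At stake is the claim that the VR programme acts through perceived control, which is its design rationale. As written, the decision rule can declare that mechanism shown when it is absent.

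**Working it through.** **Sample size per model.** The article gives 159 youths, 53 per arm, for an omnibus three-group ANOVA with alpha .05, power .80 and d=.5. With f = d/2 = .25 and the noncentral F distribution, the smallest N with equal arms is 159 (power .805), so the figure is reproduced; so are 969 and 66 for the small and large effects. Each pairwise mediation model then has 2 × 53 = 106 youths before attrition.

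**Inputs from the article.** Control shifts a₁=.34 (behaviour) and a₂=.19 (emotions), from the earlier growth mindset v supportive therapy trial cited in the Background; two simultaneous mediators; 95% bias-corrected bootstrap interval.

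**Assumptions not in the article.** Baseline control-depression correlation r from 0 to -.6; correlation between the two control scales ρ=.5; stability of control from baseline to post-intervention s_C=.7; stability of depression from baseline to 9 months s_D=.6; no attrition.

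**Expected bias.** Set the true effect of control on depression to zero and standardise all variables within arm. Each mediator then has covariance s_C·s_D·r with 9-month depression, and the two mediators correlate s_C²·ρ. Hence, for each mediator,

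b = s_C·s_D·r / (1 + s_C²·ρ) = (.7 × .6 × r) / (1 + .49 × .5) = .42r / 1.245,

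and the spurious total indirect effect is (a₁ + a₂)·b = .53·b.

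- r=-.3: b = -.101, indirect effect -.054 SD
- r=-.5: b = -.169, indirect effect -.089 SD
- r=-.6: b = -.202, indirect effect -.107 SD

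The simulated means at N=106 were -.056, -.087 and -.101; at N=2000 they were -.052, -.090 and -.108. This is bias, so a larger sample does not remove it. At N=2000 the unadjusted total indirect effect was significant in all 60 simulated trials at each r.

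**False-positive rate for the total indirect effect** (N=106, true b=0, 400 trials per setting, 1000 resamples instead of the planned 5000):

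| Shift in control | r=0 | r=-.3 | r=-.5 | r=-.6 |
|---|---|---|---|---|
| none, as written | 0.2% | 2.0% | 4.8% | 6.5% |
| .34/.19, as written | 4.8% | 14.5% | 27.2% | 32.8% |
| .34/.19, baselines added | 3.5% | 3.0% | 5.2% | 3.2% |
| .5/.5, as written | 5.2% | 30.0% | 67.8% | 75.0% |
| .5/.5, baselines added | 4.5% | 3.8% | 6.8% | 5.2% |

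The Monte Carlo standard error is √(.145 × .855/400) = 1.8 percentage points at 14.5%, and 2.2 points at 27.2%.

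**Sensitivity to stability** (r=-.5, shift .34/.19): 15.5% with s_C=.5 and s_D=.5; 30.0% with s_C=.85 and s_D=.6. With baselines added: 2.8% and 6.2%.

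**The case against.** **The article never says the models are unadjusted.** Covariates in mediation equations are often left to an analysis plan. That would carry weight if the section were a sketch. It goes down to software version, number of resamples and significance rule, and it names predictor, mediators and outcome. What it names does not match its own hypothesis about change. This is more than an unstated detail.

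**The inputs that drive the size are assumed.** This stands. The article gives no coefficient for the stability of control or for its relation to depression, and it states the inverse relation only for the PCSC, not for the SCSC. Enrolment above the 80th percentile of parent-reported CDI-2 may also weaken the correlation within the trial. At r=-.2 with the .34/.19 shift, simulation runs gave only 5% to 9%.

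**Inflation needs a real shift in control.** This also stands. With no shift the rate is at most 6.5%, and with shifts of about .1 a run at r=-.4 gave 5%. The documented .34/.19 shift is for growth mindset v supportive therapy, so it bears on that comparison most directly. No VR effect is documented. The VR v Web model is exposed to the extent that VR moves control further, as the trial hypothesises. The .5/.5 rows are therefore illustrative.

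**Mechanism is a secondary aim.** True: Aims 1 and 2 use mixed models that include the baseline assessment and are unaffected. This limits the consequence, not the error.

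**Conclusion.** The concern holds. The Aim 3 models as written do not test the stated hypothesis of change, and their control-to-depression path is confounded by baseline differences between youths. With the documented shift in control and baseline correlations of -.3 to -.5, the chance of declaring mediation when there is none is about 15% to 27% at the main stability assumptions, roughly three to five times the nominal 5%. With baselines added it stayed between 0% and 6.8% in every setting with 106 youths.

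The direction of the bias follows from an inverse control-depression relation, carry-over of control, stability of depression and an effect of condition on control. Its size rests on correlations and stabilities that the article does not report. The problem is confined to the mediation aim. How adjustment changes power to detect a real indirect effect depends on the path sizes assumed, and the conclusion does not rely on it.

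**What to change.** In all three mediation models, add baseline PCSC, baseline SCSC and baseline youth-report CDI-2 as covariates in both mediator equations and in the 9-month CDI-2 equation. State that the mediators are the post-intervention PCSC and SCSC scores, since these are the control scales in Table 2, and base the Aim 3 conclusion on the baseline-adjusted indirect effects. If change scores are preferred, justify that choice.

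Also state the remaining assumption that, given condition and the baseline scores, nothing unmeasured affects both post-intervention control and later depression. Baseline adjustment does not remove other confounding of that path, so a significant indirect effect should be reported as consistent with mediation and not as proof of it.

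The cost is a few sentences of analysis text and three covariates already collected. No new data, visits or participants are needed. The change should be fixed before outcome data are analysed.
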